#### 2.12.4 Resting-state fMRI data analysis

Functional series will be realigned (6-dof) and distortion-corrected with the reversed phase-encode pair (TOPUP), co-registered to each participant’s T1, normalized to MNI152NLin2009cAsym, and smoothed with a 6-mm FWHM kernel. Echoes will be T2*-weighted optimally combined and denoised with ME-ICA (tedana), retaining BOLD-like components. Nuisance regression will model 6 motion parameters and their derivatives plus WM/CSF aCompCor components; high-motion volumes will be flagged as spikes when FD > 0.5 mm or DVARS exceeds the dataset-specific distribution. Band-pass filtering (0.008–0.09 Hz) will be applied within the same general linear model to avoid reintroducing noise. Datasets with mean FD > 0.2 mm or >20% censored volumes will be excluded. Global signal regression will not be used in the primary analysis given ongoing debate; identical models with GSR will be run as a sensitivity check.

Connectivity analyses will center on bilateral DLPFC seeds placed at the stimulation site (6-mm spheres in MNI space, inverse-warped to native to form subject-specific masks). *A priori* ROIs will further include sgACC, PCC/precuneus (DMN), anterior insula/dACC (salience), and intraparietal/inferior parietal nodes (frontoparietal/executive). For each seed, subject-level Pearson correlation maps will be Fisher-z transformed and averaged across runs; ROI-to-ROI z-transformed matrices will also be computed using the Schaefer parcellation and Yeo networks (Fox et al., 2005; Yeo et al., 2011; Schaefer et al., 2018). To improve specificity, all connectivity will be estimated after nuisance regression and scrubbing; where appropriate, surface-based analyses in fsaverage will additionally be performed. As secondary endpoints, we will summarize graph metrics (global/local efficiency, modularity, participation coefficient) from the ROI graphs.

Primary within-subject contrasts will evaluate pre- vs. post-stimulation changes in (i) DLPFC-sgACC coupling (*a priori* expectation: stronger anticorrelation post-stimulation), (ii) DLPFC interactions with executive and default-mode networks (hypothesized ECN-DMN rebalancing), and (iii) whole-brain seed-to-voxel effects from the stimulated DLPFC. Group inference will use mixed-effects GLMs; voxelwise maps will be thresholded with permutation testing (≥5,000 permutations, TFCE), and ROI-level tests will controll FDR *q* < 0.05. We will report effect sizes for paired contrasts (Cohen’s dz) and 95% CIs. Robustness will be assessed by repeating models with/without GSR and by varying DLPFC seed radius (4 - 8 mm).

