Electroencephalography will be used to monitor cortical activity during ultrasound neuromodulation of the DLPFC at baseline, 2 weeks, and 4 weeks (Schlögl et al., 2016). Resting-state signals will be recorded continuously for 5 min before stimulation (baseline) and for 5 min immediately after stimulation. A 64-channel cap configured according to the international 10–20 system will be used, sampled at 1,000 Hz with electrode impedances kept <5 kΩ.

fMRI Acquisition

Functional magnetic resonance imaging will be used to evaluate changes in brain structure and connectivity. Scans will be performed at baseline and 4 weeks (Schlögl et al., 2016). Scanning will be performed on a 3T scanner with a 32-channel receive head coil. Each participant will first undergo high-resolution structural imaging for anatomical reference and spatial normalization. A multi-echo T1-weighted MPRAGE volume will be acquired (0.8 mm isotropic; TR = 2,500 ms; TEs = 1.81/3.60/5.39/7.18 ms; TI = 1,000 ms; flip angle = 8°; FOV = 256 mm; in-plane acceleration = 2), followed by a T2-weighted scan matched in resolution (0.8 mm isotropic; TR = 3,200 ms; TE = 564 ms; FOV = 256 mm; acceleration = 2). Auto-alignment to the AC-PC plane and vendor-supplied B0 shimming will be used prior to acquisition.

Resting-state fMRI will be collected with a multi-echo, multi-band gradient-echo EPI sequence (2.5 mm isotropic; TR = 1,670 ms; TEs = 15.6/38.2/60.8/83.4 ms; multiband factor = 4; in-plane acceleration = 2; echo spacing = 0.50 ms). To enable susceptibility-distortion correction, two runs (∼9 min, ∼300 volumes each) will be acquired with reversed phase-encoding directions (A→P and P→A) while keeping all other parameters identical. Participants will be instructed to keep their eyes open, fixate a central cross on a black background, remain awake, and minimize overt cognitive strategies. Head motion will be reduced using foam padding and a forehead strap; MR-compatible headphones/earplugs will provide acoustic attenuation.

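### At the accepted 20% censoring limit, the single-GLM fMRI denoising model leaves about 0 to 10 residual degrees of freedom per run, so the retention rule should be set on residual df

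*Protocol article*

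**What the plan says.** Section 2.9.2 fixes the acquisition. The repetition time is in "TR = 1,670 ms; TEs = 15.6/38.2/60.8/83.4 ms", and the amount of data is given as "two runs (∼9 min, ∼300 volumes each) will be acquired with reversed phase-encoding directions".

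Section 2.12.4 fixes the denoising model:
- Regressors: "Nuisance regression will model 6 motion parameters and their derivatives plus WM/CSF aCompCor components". The number of components is not given.
- Censoring: "high-motion volumes will be flagged as spikes when FD > 0.5 mm or DVARS exceeds the dataset-specific distribution".
- Filtering: "Band-pass filtering (0.008–0.09 Hz) will be applied within the same general linear model to avoid reintroducing noise".
- Retention: "Datasets with mean FD > 0.2 mm or >20% censored volumes will be excluded".

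The same section estimates all connectivity after this regression and scrubbing. It forms Fisher-z correlation maps and averages them over the runs, so each run has to support a correlation of its own. It names DLPFC–sgACC coupling, DLPFC interactions with the executive and default-mode networks, and seed-to-voxel change as the main within-subject contrasts. Table 2 lists fMRI as a secondary outcome.

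**The concern.** Filtering inside the regression is sound practice, but it is not free. Each frequency removed costs a column for its sine and one for its cosine, and at this TR most of the spectrum lies outside 0.008–0.09 Hz. Each censored volume costs one further df, whether it enters as a spike regressor or is deleted. A limit of 20% sounds as if 80% of the information survives. In fact the spikes are charged against the minority of df that the filter left.

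At stake are the connectivity contrasts and the graph metrics built from the same matrices. A run near the limit passes quality control as valid, yet its z values carry little or no information. Precision also varies with motion between participants, between a participant's two visits and between the two runs of one visit, while equal averaging treats all runs alike.

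**Working it through.** **Inputs.** From section 2.9.2: TR 1.67 s and about 300 volumes per run. From section 2.12.4: pass-band 0.008–0.09 Hz in the model, 6 motion parameters plus derivatives = 12 terms, one df per flagged volume, and up to 20% censored. Assumed: 0 to 20 aCompCor components, and the 20% limit read as applying to each run.

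**The plan's own figure.** 300 × 1.67 s = 501 s = 8.35 min. A full 9 min gives 540 / 1.67 = 323 volumes. The two approximate figures agree only within rounding, so both are carried forward.

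**Cost of the filter (300 volumes).** Frequencies are spaced 1/501 Hz apart. The pass-band runs from index 5 (0.008 × 501 = 4.01) to index 45 (0.09 × 501 = 45.09), which is 41 frequencies or 82 dimensions. The filter uses 300 − 82 = 218 df, or 73%. A discrete cosine basis also keeps 82.

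**Residual df at the 20% limit (60 scattered spikes).**
- Filter and spikes: 300 − 218 − 60 = 22
- Less 12 motion terms: 10
- Less 5 aCompCor components: 5
- Less 10 aCompCor components: 0

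**Residual df per 300-volume run.** Formula: 82 − 12 − K − spikes, floored at 0. It was confirmed by the rank of simulated design matrices.

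| aCompCor components (K, assumed) | 0% | 5% | 10% | 15% | 20% |
|---|---|---|---|---|---|
| 0 | 70 | 55 | 40 | 25 | 10 |
| 5 | 65 | 50 | 35 | 20 | 5 |
| 10 | 60 | 45 | 30 | 15 | 0 |
| 20 | 50 | 35 | 20 | 5 | 0 |

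**With 323 volumes.** The pass-band keeps 88 dimensions, and at most 64 volumes can be censored (20% of 323 is 64.6). That leaves 88 − 64 − 12 = 12 before aCompCor, 7 with 5 components, 2 with 10 and 0 with 20. The cosine basis gives one more in each of the first three cases.

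**Precision.** The approximate standard error of Fisher z in one run is 1/√(df − 2): 0.13 at 60 df, 0.19 at 30, 0.28 at 15, 0.35 at 10 and 0.58 at 5. It is undefined at 2 df or fewer. For the mean of two equal, independent runs, divide by √2: 0.09, 0.13, 0.20, 0.25 and 0.41.

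**Effect of equal averaging.** Take one run with 60 df and one with 5. The equal average has standard error ½√(1/58 + 1/3) = 0.30, worse than the good run alone (0.13). Weighting by residual df gives √(60²/58 + 5²/3)/65 = 0.13.

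**Can the limit be reached?** If 20% of volumes lie just above FD 0.5 mm, they contribute 0.2 × 0.5 = 0.10 mm to the mean. Mean FD stays within 0.2 mm if the other 80% average at most 0.10 / 0.8 = 0.125 mm. DVARS flags can also add censored volumes.

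**Spike placement.** Spikes in long contiguous blocks overlap numerically with the filter columns. For 60 spikes in blocks of 20 to 60 volumes, about 41 to 50 dimensions remain after filter and spikes instead of 22, although the fit is ill-conditioned. Blocks of 5 still leave 22.

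**The case against.** A reader might infer that the filter and the spikes alone exhaust a run, or that connectivity cannot be measured in the retained scans. The documents support neither. Filter plus spikes leave 22 df, and zero also needs the 12 motion terms and 10 components, a number the article does not give. With 10 components, scans with up to 10% censoring keep 30 to 60 df per run, which is workable, and averaging two runs improves the precision further.

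Three further points count against a broad claim. The mean-FD limit restricts who can reach 20% through displacement, since such a participant must be quite still for the rest of the run, and section 2.9.2 plans padding and a forehead strap. Clustered motion leaves more rank than scattered motion. Modelling both runs jointly with shared nuisance terms would leave about 164 − 120 − 22 = 22 df at the limit with 10 components, but the article averages maps across runs instead.

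It can also be said that the component count and a minimum-df check belong in the full protocol or in the manual of operations promised in section 2.13. That is fair for the count on its own. It does not answer the point, because the article itself states the retention limit, and that limit conflicts with the model it states: even with no components at all, 10 df per run remain.

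**Conclusion.** The point holds for scans at or near the 20% limit. There, a run of about 300 volumes with scattered spikes has at most about 10 residual df, about 5 with 5 components and none with 10; a 323-volume run with 10 components has about 2. Seed correlations from such runs are undefined or nearly pure noise, yet the stated rule keeps them and averages them at full weight.

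The size rests on the assumed component count, on scattered spikes and on run-wise modelling. Any df removed by ME-ICA would lower the figures further. How many scans will fall near the limit cannot be derived from the documents. The fMRI contrasts are secondary, so the Go/No-go primary outcome and the sample size are untouched. The change is worth making before the data are analysed, but it does not threaten the trial's main conclusion.

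**What to change.** In section 2.12.4:
1. Keep the mean-FD limit. Replace or supplement the 20% censoring limit with a pre-specified minimum residual df per run, counted after the full model (filter, motion, aCompCor and spikes).
2. State the number of aCompCor components, since the minimum has no meaning without it.
3. Weight the two runs by residual df when averaging Fisher z.
4. Report residual df by arm and visit.

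The minimum is the team's choice. A floor of 30, as an example only, amounts to a 10% censoring cap for 300 volumes with 10 components and gives a per-run standard error of about 0.19.

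Dropping the 0.09 Hz low-pass would leave about 209 df at 20% censoring with 10 components (300 − 9 high-pass and constant terms − 12 − 10 − 60). It changes the chosen frequency band and lets in higher-frequency noise, so it should be at most an optional sensitivity analysis.

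The cost is analysis wording only, plus the possible loss of a few more high-motion scans.

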### 2.7 Intervention

Participants will perform LIPUS therapy independently at home over a 4-week period, utilizing a self-developed wearable device (Figure 2). The LIPUS group will receive pulsed therapeutic ultrasound, targeting the bilateral DLPFC projections on the scalp. The LIPUS device operates at a frequency of 600 kHz with an effective intensity of 1.0 W/cm^2^ and a 50% duty cycle (10 ms on, 10 ms off). Two transducers work alternately (each active for 1 s) during a 20-min treatment session, maintaining the treatment-site temperature below 41 °C to ensure safe and stable acoustic stimulation (Hayner and Hynynen, 2001; Zhang et al., 2021; U.S. Food and Drug Administration, 2019; Fomenko et al., 2020; Legon et al., 2020; Pellow et al., 2024). Each session will last 20 min, performed daily over 4 weeks. Treatment settings will remain unchanged throughout the trial unless the participant’s condition worsens or adverse effects are observed. The sham group will use a device identical in appearance and operation to the LIPUS group’s device but delivering no therapeutic ultrasound. All participants, regardless of group allocation, will receive standardized guidance on a low-calorie diet and maintenance of their habitual physical activity. This guidance is consistent with participants’ usual routines, and no additional dietary or exercise interventions will be applied. Participants will remain at home throughout the study, and will be asked to maintain daily logs of food intake and physical activity, which will be collected and reviewed regularly by the study team throughout the study period, ensuring that any observed differences in outcomes can be attributed to LIPUS stimulation.

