### 2.12 Analysis plan

#### 2.12.1 Statistical analysis

Data will be processed and analyzed using SPSS 26.0. Continuous data will be summarized as means and standard deviations if they follow a normal distribution; otherwise, medians and interquartile ranges will be reported. Categorical variables will be presented as frequencies and percentages. To compare continuous data between groups, independent samples *t*-tests will be used for normally distributed variables, while non-parametric tests will be applied for data that do not meet normality assumptions. For categorical data, group differences in proportions will be assessed using chi-square tests or Fisher’s exact test, depending on the data characteristics. A repeated-measures ANOVA will be conducted to evaluate outcome variables between the two groups across the three assessment time points. For the primary outcome, measured by the food Go/No-Go task, will be analyzed using an intention-to-treat approach, which includes all randomized participants. Sensitivity analyses will be conducted using per-protocol sets to examine data from participants who completed the trial as planned and adhered to the protocol, as well as full analysis sets to evaluate the robustness and generalizability of the results. Additionally, safety sets will be utilized to analyze adverse events throughout the trial.

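### The fMRI section names only within-subject pre/post contrasts and paired effect sizes, and specifies no LIPUS-versus-sham contrast, so a change common to both arms could not be told apart from a LIPUS effect

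*Protocol article*

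**What the plan says.** Section 2.12.4 sets out the inference for resting-state fMRI:

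- **Contrasts.** "Primary within-subject contrasts will evaluate pre- vs. post-stimulation changes in (i) DLPFC-sgACC coupling". Items (ii) and (iii), on DLPFC interactions with the executive and default-mode networks and on whole-brain seed-to-voxel effects, fall under the same opening.
- **Group level.** "Group inference will use mixed-effects GLMs", with no fixed effects listed.
- **Multiplicity.** Voxelwise maps use permutation testing with TFCE. For regions of interest, "ROI-level tests will controll FDR" at q < 0.05.
- **Effect size.** "We will report effect sizes for paired contrasts", namely Cohen's dz, with 95% confidence intervals.

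Section 2.12.4 does not mention sham, arm or an arm-by-visit term.

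Other relevant places:

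- Table 2 lists fMRI as a secondary outcome. Section 2.9.2 gives its timing: "Scans will be performed at baseline and 4 weeks".
- Section 2.12.1 plans a repeated-measures ANOVA "to evaluate outcome variables between the two groups across the three assessment time points". It also has a generic provision for two-sample t-tests or non-parametric tests of continuous data.
- Section 2.9.1 defines the primary outcome as a LIPUS-versus-sham difference in change.
- Section 2.7: "All participants, regardless of group allocation, will receive standardized guidance on a low-calorie diet". Both arms also keep food and activity logs and use devices of identical appearance. Section 2.6 says that all devices have a vibration mode.

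**The concern.** The trial is randomized 1:1 against sham, so that whatever happens to everyone over four weeks cancels in the comparison of arms. A pre/post contrast does not use that protection. Between the two scans, both arms are scanned a second time, receive diet guidance, log food and activity, and wear a vibrating device daily. Any of these might move DLPFC connectivity, and a within-subject contrast would pick it up whether or not ultrasound does anything.

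The abstract expects the neuroimaging to help provide evidence for a neuromodulatory role of LIPUS. That is a causal claim, and it needs the sham comparison. The authors wrote that comparison out for the primary outcome but not for fMRI, although the fMRI section is detailed enough to fix seed radius, permutation count, motion cut-offs and a sensitivity analysis for global signal regression. An analysis that followed section 2.12.4 literally would not use the randomized comparison for this outcome.

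**Working it through.** **1. Does any other text supply the between-arm contrast?**

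| Text | What it offers | Does it specify LIPUS versus sham for fMRI change? |
|---|---|---|
| 2.12.4, contrasts (i)-(iii) | pre versus post, within subject | No |
| 2.12.4, mixed-effects GLM | a class of model | Could hold an arm-by-visit term; none is named |
| 2.12.4, effect size | paired dz | No |
| 2.12.1, ANOVA | two groups, three time points | Between groups, but fMRI has two time points (2.9.2, Table 1) |
| 2.12.1, t-tests | two groups, any continuous variable | Could be applied to fMRI change; not tied to it |

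**2. Inputs for an illustration.** The document gives no sample size or expected effect for fMRI.

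- n = 20 per arm, from section 2.11. This figure belongs to the primary outcome and reproduces as a two-group, two-measurement interaction test with f = 0.25, correlation 0.4 and N = 40: noncentrality 0.25² × 40 × 2 / (1 − 0.4) = 8.33, df 1 and 38, power 0.803. Adding 10% gives 40 × 1.1 = 44. It has no bearing on the fMRI point beyond supplying n.
- Two-sided 5% level, from section 2.11.
- Assumptions: no LIPUS effect; the same standardized change dz (mean change divided by the SD of change) in both arms, ranging from 0.3 to 0.6; one test, with no TFCE or FDR adjustment.

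**3. Formulas.** The paired test on n participants has df = n − 1 and noncentrality dz × √n. Its rejection probability is the mass of the noncentral t beyond ±t(0.975, df). The critical values are 2.093 for n = 20 and 2.023 for n = 40. For example, at dz = 0.5 the noncentrality is 0.5 × √20 = 2.24 in one arm and 0.5 × √40 = 3.16 with both arms pooled.

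If each arm were tested separately, the chance of a significant result in LIPUS but not in sham is p × (1 − p), where p is the one-arm rejection probability.

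A two-sample test of change has noncentrality zero here, because the shared change cancels. It rejects in 5% whatever dz is.

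**4. Results.**

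| Shared dz | LIPUS arm, paired (n = 20) | Both arms pooled, paired (n = 40) | LIPUS significant, sham not: p(1 − p) | Between-arm test of change |
|---|---|---|---|---|
| 0.3 | 0.247 | 0.457 | 0.247 × 0.753 = 0.186 | 0.05 |
| 0.4 | 0.397 | 0.694 | 0.397 × 0.603 = 0.239 | 0.05 |
| 0.5 | 0.565 | 0.869 | 0.565 × 0.435 = 0.246 | 0.05 |
| 0.6 | 0.721 | 0.959 | 0.721 × 0.279 = 0.201 | 0.05 |

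Simulation (40,000 runs) at dz 0.3 and 0.5 agreed: 0.249 and 0.563 for the LIPUS arm, 0.460 and 0.871 pooled, and 0.05 between arms.

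The product p(1 − p) cannot exceed 0.25, so the discordance column should be read as a range of about 19% to 25%.

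**The case against.** The best reply is that the section is silent on arm and does not exclude it. In two-level imaging analysis, post minus pre is often the subject-level quantity carried into a group model, and that model may contain arm. The generic t-tests in section 2.12.1 could also be run on Fisher-z change and need only two scans. Both points stand as possibilities, so the accurate statement is that no between-arm contrast is specified. They do not settle the matter: the section designates the within-subject contrasts as primary, promises only the paired effect size, and names no arm term.

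A reader might infer that a shared change would be reported as a LIPUS effect, or that the arms will be tested separately and their p-values compared. The document says neither. It supports only that the two explanations could not be told apart from the contrasts it names. The discordance figure applies only if the arms were tested separately.

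The size is also open to challenge. The shared dz is assumed. Section 2.7 says the guidance matches participants' usual routines and that no additional diet or exercise intervention is applied, which weakens the case for a large common change without removing it. TFCE, FDR and motion exclusions would alter the rates. They address multiplicity and data quality and do not supply a comparator.

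Finally, the word primary in section 2.12.4 ranks contrasts within the fMRI analysis. It does not make fMRI a primary endpoint of the trial.

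**Conclusion.** The concern holds in this form: section 2.12.4 makes within-subject pre/post contrasts the main fMRI inference, with paired effect sizes only, and specifies no LIPUS-versus-sham contrast for this secondary outcome. This is more than an omitted detail, because the text positively fixes a comparison that does not use the randomization.

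The size cannot be read from the document. Under the stated assumptions (no LIPUS effect, shared dz 0.3 to 0.6, 20 per arm, one unadjusted 5% test), a paired contrast is significant in roughly 25% to 72% of trials in one arm and 46% to 96% pooled, against 5% for the between-arm test. These figures show direction and scale and do not predict this trial's error rate.

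Severity is moderate. fMRI is one of several secondary outcomes, and the primary comparison of reaction-time change is unaffected.

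**What to change.** In section 2.12.4, for each of contrasts (i)-(iii), make the LIPUS-minus-sham difference in baseline-to-week-4 connectivity change the inferential contrast. Either an arm-by-visit term in the mixed-effects GLM or week-4 connectivity compared between arms with baseline connectivity as a covariate would do; name one in advance. Apply the permutation/TFCE and FDR procedures to that effect, and report its size with a 95% confidence interval. Keep within-arm pre/post changes and dz, labelled as descriptive.

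The cost is analysis wording only, with no new scans or participants. The downside is precision. In units of the SD of change, the standard error is √(2/20) = 0.316 for a between-arm difference in change, against 1/√20 = 0.224 for a one-arm paired contrast and 1/√40 = 0.158 for a pooled one. Fewer results will be significant; baseline adjustment may recover part of the loss.
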